^ has initiated a promising new era of research that could explain the benefits observed after n-3 PUFA supplementation and AEx in individuals with RA. However, whether they are responsible for this adaptive response, also remains to be elucidated.

*Research hypothesis:* N-3 PUFA and AEx will have synergistic effects on disease progression, cardiometabolic health, and quality of life in individuals with RA, and these changes will be associated with SPM production in blood and synovial fluid.

*General aim:* To investigate the effects of n-3 PUFA supplementation and AEx training on disease progression, cardiometabolic health, and quality of life and their association with the plasma and synovial fluid levels of SPMs in individuals with RA.

*Specific aims*:
(1)To compare the effects of n-3 PUFA supplementation, AEx training, and the combination of both on disease progression, cardiometabolic health, and quality of life in individuals with RA.(2)To compare the effects of n-3 PUFA supplementation, AEx, and the combination of both on the plasma and synovial fluid levels of the SPMs in individuals with RA.(3)To examine the relationship between the plasma levels of the n-3 PUFA derived SPMs with systemic disease progression, cardiometabolic health, and quality of life in individuals with RA

To achieve these aims we have designed a randomized, 16-week, placebo-controlled, blinded interventional trial.

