### Sample size

The sample size calculation for this study is based on an α level of 0.05, a power (1-β) of 0.8, and effect size of 0.42 (morning stiffness).
^
11
^ A minimum of 18 participants are necessary per group; however, 22 individuals will be recruited to account for a typical dropout rate of 20% in long-term intervention studies.

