### Study design

This study consists of a 16-week intervention with n-3 PUFAs and/or aerobic exercise (AEx) training. The subjects will be randomly assigned in a double-blinded manner to one of four groups: placebo control (PLA), PLA+AEx, n-3, or n-3+AEx. A stratified randomized assignment (by block) process will be employed to ensure that the experimental groups are balanced for disease activity, pharmacological treatment, sex, and age. The principal investigator and pharmacy personal will be aware of patient allocation and will code the information. Patients and exercise intervention supervisors will be blinded for supplement intervention, while medical specialists and database analysis personal will be blinded for supplement treatment and exercise intervention. The study will be unblinded for patients and medical specialist if the participant worsens their condition according to the criteria described below or if they decide to drop out the study.

The training sessions will be conducted at the Laboratorio de Ciencias del Ejercicio en el Ciclo Vital (Lab-CERVITAL), Universidad de O’Higgins. The week before intervention the participants will perform RA specific tests (e.g., Disease Activity Score-28) and functional measurements (e.g., handgrip strength), peak aerobic capacity test, a dietary and physical activity assessment, and blood samples will be collected. Subsequently, participants will start their 16-week intervention (PLA, PLA+AEx, n-3, or n-3+AEx). At the end of the intervention the same initial measurements, questionnaires, and assessments will be collected. In a subgroup of participants (n=24 in total or n=6 per group) extraction of synovial fluid will be performed before and after the intervention.

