### Primary and secondary outcomes

Primary outcome: Early morning stiffness is one of the main outcomes significantly improved by n-3 PUFA supplementation in RA patients.
^
11
^ Therefore, the difference in the duration (minutes) of early morning stiffness has been selected as the primary outcome to compare the intervention effect in each group after the intervention period.

Secondary outcomes: Other relevant outcomes which allow the assessment of disease progression will be measured, such as the Disease Activity Score-28, DHA-SPMs, tender and swollen joint count, quality of life, grip strength, analgesic use, and TNF-α blood levels.

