### Supplementation and exercise intervention

The participants will be supplemented with either 5 capsules per day of Omega UP (Newscience, Chile) equivalent to 2.5 g/d of DHA and 0.5 g/d of EPA or a placebo filled gelatin capsule. The current doses are within the limits recommended by the European Food Safety Authority and have been shown to be safe, to be incorporated into cell membranes, and to produce significant improvements in overall health in individuals with RA.
^
35
^
^–^
^
38
^ Capsules will be placed into de-identified bottles by people not involved in the study and provided to the participants to ensure double blinding.

Patients will be given 2-4 weeks of capsules at a time, with all capsules counted before and after this timeframe, and a small notepad will be provided for them to write down every time when the capsules are taken. Furthermore, patients will receive weekly phone calls and text messages to serve as reminders for treatment adherence. Capsule treatment will be discontinued if patients worsen their condition or if the patient decides to drop-out without questioning their decision.

The exercise intervention will be performed according to the recommendations from the European Alliance of Associations for Rheumatology (EULAR) consisting of aerobic type exercise training three times per week, on non-consecutive days, with a total time of 20-60 minutes.
^
25
^ The AEx will be performed on a stationary electronically braked cycle ergometer starting at 40-50% of VO
_2_peak for 20 minutes. The intensity and volume of cycling will then be gradually increased to target at least 60-70% of VO
_2_peak for 50-60 minutes over the final 10 weeks. Heart rate, power output and rating of perceived exertion (RPE) will be monitored during training intervention.

A brief talk about the exercise importance for their conditions will be made every first session of the week to create awareness about it. Also, sessions have been planned at moderate intensity to decrease the risk of discomfort and to improve adherence. The exercise intervention will be stopped if the patient presents any discomfort related to fatigue, consciousness, cardiac, respiratory, or muscular hassle. Furthermore, if at some point disease symptoms are an obstacle for exercise practice, the patient will be advised to drop out the study. Finally, all patients in the exercise group may drop out from the study at any point without justification.

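### Exercise-arm patients whose disease symptoms hinder exercise are advised to leave the study, not only to stop exercising, which risks arm-specific, outcome-related loss of week-16 data

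*Protocol article*

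**What the plan says.** The section on supplementation and exercise intervention has separate rules for stopping. Discomfort during training (fatigue, consciousness, cardiac, respiratory or muscular) stops the exercise intervention. Disease symptoms are handled differently: "if at some point disease symptoms are an obstacle for exercise practice, the patient will be advised to drop out the study".

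The worsening rules that cover all four arms do not go that far. In the same section, "Capsule treatment will be discontinued if patients worsen their condition". Under Study design, "The study will be unblinded for patients and medical specialist if the participant worsens their condition". Neither advises the patient to leave.

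On timing, baseline is the week before the intervention, and then "At the end of the intervention the same initial measurements, questionnaires, and assessments will be collected". No intermediate outcome visit is described. Under Primary and secondary outcomes, "the difference in the duration (minutes) of early morning stiffness has been selected as the primary outcome"; DAS28, tender and swollen joint counts and quality of life are among the secondary outcomes. The first specific aim is "To compare the effects of n-3 PUFA supplementation, AEx training, and the combination of both on disease progression", and the hypothesis is that "N-3 PUFA and AEx will have synergistic effects on disease progression".

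**The concern.** Two patients with the same flare are handled differently because of the arm to which they were randomised. One in an exercise arm may be advised out of the study; one in PLA or n-3 gets no such advice. The Introduction names stiffness, with swelling, pain and fatigue, among the symptoms of the disease, so those advised to leave are likely to include patients heading for poor stiffness, DAS28 or joint-count results.

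If they leave before week 16, the exercise arms are compared on a selected, probably healthier, remainder. This touches four of the six pairwise comparisons between arms, namely each exercise arm against each non-exercise arm, and these belong to the first aim. A missing-data method could explore the consequences but could not supply the values that were never collected.

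**Working it through.** **The plan's own figure.** Sample size gives a minimum of 18 per group (α 0.05, power 0.8, effect size 0.42). Read as a one-way ANOVA with four groups and Cohen's f = 0.42, the smallest n is 17 (power 0.815), and 18 gives 0.840. The stated 18 is therefore reproduced closely, and the point here does not depend on it. The same section says that "22 individuals will be recruited to account for a typical dropout rate of 20% in long-term intervention studies": 22 × 0.8 = 17.6 expected completers per arm. That allowance covers loss of numbers, not loss that differs by arm and is related to outcome.

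**Inputs.**
- From the article: four arms of 22, hence 44 patients in the exercise arms; 20% dropout; ANOVA followed by Fisher's LSD; p < 0.05.
- Assumed, since the article does not give them: the share p lost through symptoms (5%, 10%, 20%), and the correlation ρ between the trigger and the change in stiffness (0.3, 0.5, 0.7). In patients, 5%, 10% and 20% of 44 are about 2, 4 and 9.

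**Bias with no true exercise effect.** If the fraction p with the worst symptoms leaves an arm, the mean of those who remain shifts towards benefit by ρ·φ(z)/(1−p) SD, where z is the upper p-quantile of the standard normal and φ its density. Example with p = 0.10: z = 1.2816, φ(z) = 0.1755, and 0.1755/0.90 = 0.195. Multiplying by 0.3, 0.5 and 0.7 gives 0.058, 0.097 and 0.136. The bias is the shift in the exercise arms minus the shift in the other arms.

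**Error rate.** A simulation of 20,000 trials per cell used 4 × 22 patients, 20% expected total loss in every arm (any loss not due to symptoms being random), no true effect, and the comparison PLA+AEx v PLA at a nominal 5%.

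| Symptom exit, exercise v other arms | Bias in SD, ρ = 0.3 / 0.5 / 0.7 | LSD error (%), not conditional on F |
|---|---|---|
| 20% v 20% | 0 / 0 / 0 | 5.2 / 5.2 / 4.8 |
| 5% v 2.5% | 0.015 / 0.024 / 0.034 | 5.0 / 5.1 / 5.1 |
| 10% v 5% | 0.026 / 0.043 / 0.061 | 5.2 / 5.1 / 5.8 |
| 20% v 10% | 0.046 / 0.077 / 0.108 | 5.1 / 5.7 / 6.6 |
| 5% v 0 | 0.033 / 0.054 / 0.076 | 5.1 / 5.2 / 5.7 |
| 10% v 0 | 0.058 / 0.097 / 0.136 | 5.1 / 5.7 / 6.9 |
| 20% v 0 | 0.105 / 0.175 / 0.245 | 6.3 / 8.2 / 11.4 |

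The simulation standard error near 5% is √(0.05 × 0.95/20,000) = 0.15 percentage points, so differences of a few tenths are noise.

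**LSD read only after a significant F-test.** The pairwise error is 1.9% with no symptom-driven loss. With loss in the exercise arms only, it is 2.0 / 1.9 / 2.3% at 5% exit, 2.0 / 2.3 / 3.0% at 10%, and 2.4 / 3.7 / 5.8% at 20%.

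**Pooled exercise comparison (44 v 44).** If the two exercise arms were pooled against the other two, with loss in the exercise arms only and a normal approximation, the error would be 5.8 / 7.4 / 9.9% at 10% exit and 7.5 / 12.5 / 20.9% at 20%. The bias is the same; the standard error is smaller.

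**Synergy contrast.** With equal exit in both exercise arms the shifts cancel, and the simulated error is 4.8–5.3%. If n-3 relieves symptoms, exit could differ: 20% in PLA+AEx against 10% in n-3+AEx gives an interaction bias of 0.05–0.11 SD.

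**The case against.** The strongest reply is that harm is not demonstrated. Every exit rate and correlation above is assumed. With half as much loss in the other arms, the pairwise error stays near nominal (5.0–6.6%), and because the article has LSD following the ANOVA, the lower figures conditional on F may be the relevant ones. The 11.4% needs 20% symptom exit in the exercise arms, which uses up the whole dropout allowance, none elsewhere, and a correlation of 0.7. This all stands and sets the priority of the point.

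The asymmetry may also be smaller than the wording suggests. A worsening PLA or n-3 patient loses the only study treatment and the blind, and may well leave unprompted. That stands too: how many would leave is not known.

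Eligibility limits how often the rule is triggered. Disease activity is moderate, drugs are stable, and patients with limitations to exercise are excluded; training is moderate, and the rule is only advice. This lowers the likely exit rate but does not remove an instruction that works against retention.

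Finally, a condensed article may leave the follow-up of patients who discontinue to a fuller document. That would answer a complaint about silence. Here the article states a rule, and by its wording the patient leaves the study, whereas the neighbouring rule only stops the exercise. Recorded dropout reasons and sensitivity analyses would help to judge the damage but would not restore the missing values.

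**Conclusion.** The concern holds as a design choice worth reconsidering. The text sends symptomatic exercise patients out of the study, gives no counterpart advice in the other two arms, and relies on a single end-of-treatment assessment. The risk is confined mainly to the four comparisons of an exercise arm with a non-exercise arm. The two n-3 comparisons within exercise level are not made asymmetric, and synergy is affected only if exit differs between the two exercise arms.

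The size cannot be determined from the article: it runs from no bias, with equal loss, to 0.24 SD at the extreme of the assumed range. The likeliest direction favours exercise, but a flare may settle by week 16, or those who leave may have had most room to improve. Confidence is medium, because the wording is clear while the frequency of the trigger and its link to the outcome are not given.

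**What to change.** Reword the sentence so that disease symptoms which prevent exercise end or reduce the exercise only, on the same clinical grounds as now. Add that in all four arms a patient who stops exercise or capsules stays in the study, is invited to the week-16 assessments that are clinically safe for them, and is analysed in the randomised arm. At a minimum these are morning stiffness, DAS28, the questionnaires and blood samples; the peak cycling test is done only with medical clearance. Follow-up ends only by the patient's decision or on a clinician's safety grounds.

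The cost is two sentences by amendment, with whatever ethics review that needs, and about 2–9 extra week-16 visits if 5–20% of the 44 exercise patients would otherwise have left, plus visits for any PLA and n-3 patients who stop capsules. There is one small downside. Patients who stopped exercising stay in the exercise arms, so the comparison estimates the effect of being assigned to exercise; the mechanistic questions may need a supplementary analysis of those who kept training.

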### Monitoring

A data monitoring committee will not be needed in this study since it has minimal risks and will be a short period of intervention. Interim analyses will be made by the principal investigator and a selected team of personnel every two weeks, indicating the total number of reported adverse events and its severity, any other undesirable effect, and the number of dropouts.

### Characterization and anthropometric measures of participants

Body mass and height will be determined with a scale and wall-mounted stadiometer. The participant’s age, body mass index (BMI), educational status, socioeconomic level, years of diagnosis, smoking habits, comorbidities, and medications will be recorded.

### RA disease progression

*Duration of morning stiffness*: This will be assessed by asking “How long is your morning stiffness from waking until maximum improvement?”.
^
39
^ The duration of morning stiffness will be reported in minutes up to a maximum of 180 minutes.

*Disease Activity Score-28 (DAS28*): Describes the severity of rheumatoid arthritis using clinical and laboratory data. It is composed of the number of swollen joints (total 28), the number of tender joints (total 28), the Westgren erythrocyte sedimentation rate (ESR), and patients’ global disease assessment through a visual analog scale (VAS). The DAS28 has been extensively validated for its use in clinical trials and it is required by the Chilean Ministry of Health.
^
40
^

*Health assessment questionnaire disability index (HAQDI):* This tool evaluates the functional status of RA individuals. It consists of eight sections: dressing, arising, eating, walking, hygiene, reach, grip, and activities, with 2 or 3 questions for each section. Scoring is from 0 (without any difficulty) to 3 (unable to do). The 8 scores of the 8 sections are summed and divided by 8. This questionnaire has been validated to be used among Chilean RA patients.
^
41
^

*Quality of life RA (QOL-RA) scale*: This scale is an RA-specific health-related quality of life instrument consisting of an 8-item scale. Each item starts with the definition of an element to be considered in rating one’s quality of life, followed by a horizontal 10-point scale anchored with 1 (very poor) at one end and 10 (excellent) at the other end. The elements are physical ability, pain, interaction with family and friends, support from family and friends, mood, tension, arthritis, and health. The higher the QOL-RA Scale score, the higher the health-related quality of life. This scale has been validated to be used in the Spanish language.
^
42
^

*Analgesic use*: Analgesic use will be measured using pill counts for paracetamol and NSAIDs.

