### Participants

88 individuals (18-65 y) with rheumatoid arthritis (RA) will be recruited via newspaper advertisements, posters, flyers, visits to local community centers, and referrals from associated centers and Rheumatologists. All participants will obtain medical clearance from their Rheumatologist before taking part in the study. Individuals with moderate disease activity, as defined by the Disease Activity Score 28 (DAS28) > 2.6 and < 5.1 will be included. Participants taking nonsteroidal anti-inflammatory drugs (NSAIDs), glucocorticoids, or disease-modifying anti-rheumatic drugs (DMARDs) will be eligible; however, the dosages of these agents must be constant at least four weeks before, must remain within this limit throughout the study, and prednisone dose should not be higher than 7.5 mg/d.
^
32
^ Individuals diagnosed with gastrointestinal or metabolic diseases, regular alcohol abuse, smokers, and dietary supplement intake (e.g., fish oil capsules) or consumption of fish > 2 times per week will be excluded. Further, individuals that perform regular aerobic exercise (> 150 min moderate intensity per week) or have any physical or biomechanical limitations to complete the exercise program will also be excluded. Finally, subjects will be excluded if they present blood levels of aspartate aminotransferase, alanine transaminase, or creatinine higher than 1.5 times the maximum normal limit and total bilirubin levels of more than 1.8 mg/dL.
^
33
^
^,^
^
34
^ Participants will be encouraged to continue with their everyday normal activities. They will be fully informed of the nature and possible risks of the experimental procedures before providing their written informed consent. Participation in this study is voluntary.

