### Statistical analysis

Results will be expressed as mean ± SD. A two-way ANOVA with repeated measures followed by Fisher’s least significant difference post-test for multiple comparisons between groups will be used. Linear regression models will be constructed to examine the association between SPMs and clinical, functional, and health parameters, accounting for participant age, sex, and BMI as covariates. A value of p<0.05 will be considered statistically significant.

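### Morning stiffness, the primary outcome, is to be compared by repeated-measures ANOVA on minutes without baseline adjustment, which loses power on a duration that is probably skewed

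*Protocol article*

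**What the plan says.** All references are to the protocol article.

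- **Primary and secondary outcomes:** "the difference in the duration (minutes) of early morning stiffness has been selected as the primary outcome".
- **RA disease progression:** the value comes from a single recall question. "The duration of morning stiffness will be reported in minutes up to a maximum of 180 minutes". The lower limit of 0 is not written but follows from its being a duration.
- **Study design:** the same measurements are taken in the week before the intervention and at its end, so a baseline value exists for every participant.
- **Statistical analysis:** "Results will be expressed as mean ± SD", with group comparison by "A two-way ANOVA with repeated measures" and Fisher's LSD afterwards. No transformation, rank method or baseline covariate is named for this comparison. Age, sex and BMI appear only in the regressions on SPMs.
- **Sample size:** the calculation is "based on an α level of 0.05, a power (1-β) of 0.8, and effect size of 0.42 (morning stiffness"). It gives 18 per group, with 22 recruited. No SD and no difference in minutes is stated.

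**The concern.** With two time points, the group-by-time term of a repeated-measures ANOVA is the same test as an ANOVA on the change scores. Change scores subtract the whole baseline value. When baseline and follow-up are only moderately correlated, this adds noise that a baseline-adjusted model would not. If durations are right-skewed, as a quantity bounded at 0 often is, a few long values also inflate the error variance on the minute scale, and mean ± SD describes the data poorly.

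At stake is power for the one primary outcome in a four-arm trial that plans for 18 evaluable participants per arm. The validity of the test is not at stake.

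**Working it through.** **1. The plan's own figure.** Read 0.42 as Cohen's f with 4 groups, a 3-df test and alpha 0.05. At 18 per group the noncentrality is 0.42² × 72 = 12.7 and power is 0.84. At 17 per group power is 0.815. The stated 18 is therefore reproduced to within one participant per group. The calculation does not use a distribution in minutes, so it cannot show how the planned test would behave on skewed durations.

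**2. Why adjustment helps.** With equal variance σ² at both times and correlation ρ:

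- variance of change = 2σ²(1 − ρ)
- residual variance after adjusting for baseline = σ²(1 − ρ²)
- ratio (adjusted to change) = (1 + ρ)/2

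For log-normal durations with log-scale correlation 0.6 and log-SD s, the correlation in minutes (before capping) is (exp(0.6s²) − 1)/(exp(s²) − 1).

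| log-SD | correlation in minutes | ratio |
|---|---|---|
| 0.7 | 0.342/0.632 = 0.54 | 0.77 |
| 1.0 | 0.822/1.718 = 0.48 | 0.74 |
| 1.3 | 1.757/4.419 = 0.40 | 0.70 |

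Adjustment thus removes roughly a quarter of the error variance, and more as skew grows.

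**3. Simulated power.** Assumed, because the documents do not say: log-normal durations, median 45 min, correlation 0.6 on the log scale, 40% reduction, values rounded to 5 min. From the plan: 4 × 18 participants and the cap at 180. The test is the n-3 main effect, 36 v 36.

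| log-SD | raw change | ANCOVA, minutes | ANCOVA, log(1+min) | gain from adjustment | further gain from log |
|---|---|---|---|---|---|
| 0.7 | 74% | 91% | 96% | 17 | 5 |
| 1.0 | 48% | 63% | 73% | 15 | 10 |
| 1.3 | 33% | 43% | 50% | 10 | 7 |

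Independent runs of the same scenario differ by about 2 points (74% and 76% for raw change at log-SD 0.7). Over medians of 45-90 min the ranges are 33-84%, 43-93% and 47-96%. Type I error was 4.5-5.6% for every method.

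**4. Where the gain comes from.** Taken in this order, adjustment gives about 9-17 points with no zeros, and the log or rank scale adds about 0-11. At median 90 the rank scale adds 0-3 points (66% to 69% at log-SD 1.0). With 20% at zero, median 45 and log-SD 1.0, raw change, raw ANCOVA and rank ANCOVA give 39%, 51% and 55%, so the rank scale adds 4.

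The two gains overlap. In a 3-df four-group comparison (18 per group, reductions 0/25/25/50%, median 45, log-SD 0.6, correlation 0.5, no zeros) power was:

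- 53% for raw repeated-measures ANOVA
- 83% for raw ANCOVA
- 82% for the repeated-measures ANOVA on logs
- 92% for ANCOVA on logs

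**5. The cap.** In the step 3 scenario, raw-change power with and without the 180-minute cap was 74% v 68%, 48% v 32% and 33% v 16% at log-SD 0.7, 1.0 and 1.3.

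**The case against.** **Minutes are inferred.** The Statistical analysis section is one general statement for all outcomes in a condensed article. It does not say untransformed, and a fuller plan could add a transformation. This stands for the scale. It stands less for the model: the article does name the test and the summary, and that test has no baseline term.

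**The size is assumed.** No SD, median, skew or share at zero is given. This stands in full. The direction was the same in the scenarios tried, but the size cannot be taken from the documents.

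**It is a matter of efficiency, and minutes are easy to read.** This also stands. No stated figure is wrong, type I error is held, and a log or rank effect is harder to interpret. A baseline-adjusted analysis in minutes nevertheless gains power without giving up the unit.

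**Two stronger readings are not supported.**

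- A reader might infer that the 180-minute cap hides change and costs power. Step 5 shows the opposite for the planned test: the cap trims the long tail.
- A reader might infer that participants with no stiffness undermine the trial and that a minimum at entry is needed. Entry is indeed by DAS28 ("Individuals with moderate disease activity, as defined by the Disease Activity Score 28 (DAS28) > 2.6 and < 5.1 will be included"), and the listed components of that score do not include stiffness, so someone with 0 minutes can enrol. But the documents do not say how many would. Zeros dilute the effect on any scale, so they are no argument against this particular analysis, and an entry minimum is a design trade-off rather than a correction.

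**Conclusion.** The concern holds as one of efficiency. For a bounded and probably right-skewed duration, the stated repeated-measures ANOVA without baseline adjustment is a weaker choice than a baseline-adjusted model that uses data already collected. Under the stated assumptions, adjustment on the minute scale recovers about 9-17 points of power when nobody is at zero. A log or rank scale then adds about 0-11 points, and little when the median is higher or many participants are at zero. Mean ± SD alone would also describe a skewed outcome poorly.

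The point does not show a validity problem or a measured loss in this trial. If stiffness in this population turned out to be near-symmetric, the case for a log or rank scale would largely go. The case for baseline adjustment would remain, because the ratio in step 2 is below 1 for any correlation below 1.

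**What to change.** In the Statistical analysis section:

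1. Make the primary analysis an ANCOVA of week-16 morning stiffness, with the two factors (n-3 and AEx) and baseline stiffness as covariate.
2. Pre-specify log(1+minutes) or ranks, with baseline on the same scale, as the analysis scale if the data are skewed as expected. Settle the choice before unblinding.
3. Keep the baseline-adjusted estimate in minutes as a companion analysis, so that the result can be read in the unit of the outcome.
4. Report median and IQR beside mean ± SD for this outcome.

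The cost is wording only, with no new data and no extra participants. The one real drawback is that a log or rank effect is less direct to read, which item 3 covers.
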